# A cluster randomized controlled trial for assessing POC-CCA test based praziquantel treatment for schistosomiasis control in pregnant women and their young children: study protocol of the freeBILy clinical trial in Madagascar

**DOI:** 10.1186/s13063-021-05769-6

**Published:** 2021-11-20

**Keywords:** Schistosomiasis, Pregnant women, Children, Mass drug administration, Praziquantel, Point of care-circulating cathodic antigen test, Test-based schistosomiasis treatment, Cluster randomized controlled trial

## Abstract

**Background:**

Mass drug administration (MDA) of praziquantel is one of the main control measures against human schistosomiasis. Although there are claims for including pregnant women, infants and children under the age of 5 years in high-endemic regions in MDA campaigns, they are usually not treated without a diagnosis. Diagnostic tools identifying infections at the primary health care centre (PHCC) level could therefore help to integrate these vulnerable groups into control programmes. freeBILy (fast and reliable easy-to-use-diagnostics for eliminating bilharzia in young children and mothers) is an international consortium focused on implementing and evaluating new schistosomiasis diagnostic strategies. In Madagascar, the study aims to determine the effectiveness of a test-based schistosomiasis treatment (TBST) strategy for pregnant women and their infants and children up until the age of 2 years.

**Methods:**

A two-armed, cluster-randomized, controlled phase III trial including 5200 women and their offspring assesses the impact of TBST on child growth and maternal haemoglobin in areas of medium to high endemicity of *Schistosoma mansoni*. The participants are being tested with the point of care-circulating cathodic antigen (POC-CCA) test, a commercially available urine-based non-invasive rapid diagnostic test for schistosomiasis. In the intervention arm, a POC-CCA-TBST strategy is offered to women during pregnancy and 9 months after delivery, for their infants at 9 months of age. In the control arm, study visit procedures are the same, but without the POC-CCA-TBST procedure. All participants are being offered the POC-CCA-TBST 24 months after delivery. This trial is being integrated into the routine maternal and child primary health care programmes at 40 different PHCC in Madagascar’s highlands. The purpose of the trial is to assess the effectiveness of the POC-CCA-TBST for controlling schistosomiasis in young children and mothers.

**Discussion:**

This trial assesses a strategy to integrate pregnant women and their children under the age of 2 years into schistosomiasis control programmes using rapid diagnostic tests. It includes local capacity building for clinical trials and large-scale intervention research.

**Trial registration:**

Pan-African Clinical Trial Register PACTR201905784271304. Retrospectively registered on 15 May 2019

## Introduction

Human schistosomiasis is a neglected tropical disease (NTD) caused by trematode flatworms [1]. Among the NTDs, schistosomiasis ranks highest in terms of disability-adjusted life years (3.3 million DALYs), with more than 230 million people infected and 600 million being at risk of infection worldwide [2]. It is of particular public health importance in Africa where both intestinal and urinary forms of the disease caused by *Schistosoma mansoni* and *Schistosoma haematobium*, respectively, are prevalent. Schistosomiasis is endemic in 76 countries, and 85% of people infected live in rural areas of sub-Saharan Africa [3]. Madagascar is one of the most affected countries [4]. To reduce morbidity, the WHO recommends annual treatment of school-age children with praziquantel (PZQ) in areas of high endemicity. This is often put into practice via mass drug dministration (MDA) campaigns [5]. MDA strategies, however, have some limitations: usually, MDA focuses on school-age children, thus excluding large groups of the affected population from treatment, such as adults, pregnant women and children under the age of 5 years (U5) [6].

The main public health impact of *Schistosoma* infections is associated with chronic evolutions of the disease. Chronic infections with *S. mansoni* can lead to hepatic inflammation that progresses to advanced hepatic disease and can culminate in cirrhosis or cancer [7]. Chronic infections with *S. hematobium* can lead to ectopic pregnancy, infertility, abortion and cervical lesions and symptoms mimicking cervical cancer (female genital schistosomiasis (FGS)) [8]. All schistosomiasis infections can lead to chronic, not-organ-specific symptoms such as anaemia, fatigue and nausea. In children, schistosomiasis manifests unspecifically but equally detrimental with failure to thrive. In pregnant women, schistosomiasis may lead to anaemia.

The scientific community and WHO recognize the need for a holistic and integrated approach as the most effective way to tackle the disease [9]. Unfortunately, the exclusion of adults, pregnant women, infants and U5 children from MDA leads to increased morbidity, the perpetuation of poverty and a of schistosomiasis transmission [5].

Guidelines for the treatment of schistosomiasis during pregnancy are not yet widely implemented. After more than 30 years of post-market experience with praziquantel, no reports of serious adverse events relevant to human pregnancy have ever been published, but results from randomized controlled trials (RCTs) assessing the efficacy and safety of the drug within this target group are scarce [10]. Recent recommendations of the WHO state that schistosomiasis in pregnant women is harmful and signifies an indication for treatment. Likewise, U5 children should be given PZQ if a *Schistosoma* infection can be confirmed by a diagnostic test [5]. Effective diagnostics available at the primary level of care to detect infection are rarely integrated within the health services of the most affected countries [11]. Since 2008, a point of care (POC) rapid diagnostic test (RDT) based on the detection of the schistosome circulating cathodic antigen (CCA) [10], POC-CCA, became commercially available and is widely evaluated in various endemic settings [12–15]. The introduction of this type of tests at the primary level of care could address the treatment of vulnerable groups, if its use in the context of a dedicated strategy can be shown to be effective.

In order to improve the diagnostic strategies for the management of schistosomiasis in vulnerable groups, the international consortium freeBILy (fast and reliable easy-to-use-diagnostics for eliminating bilharzia in young children and mothers) was initiated [16]. The freeBILy consortium carries out two conceptually different trials, one in Madagascar (Universities of Antananarivo and Fianarantsoa and *Centre d’Infectiologie Charles Mérieux*) and the other one in Gabon (*Centre de Recherches Médicales de Lambaréné*) in collaboration with the Bernhard Nocht Institute for Tropical Medicine (BNITM), the Barcelona Institute for Global Health (ISGlobal), the Eberhard Karls Universität of Tübingen and the Leiden University Medical Center.

The freeBILy trial in rural Madagascar is a phase III cluster RCT (CRCT). This CRCT aims to determine the effectiveness of test-based schistosomiasis treatment (TBST) using POC-CCA for pregnant women and their infants. A cost-effectiveness analysis accompanies the trial and compares costs and health impact associated with TBST with the status quo. The cost-effectiveness will generate knowledge in the context of very few economic evaluations conducted on human schistosomiasis interventions [17].

## Methods

### Study objectives

The overall purpose of freeBILy in Madagascar is to integrate a POC-CCA test-based schistosomiasis treatment (TBST) into routine maternal and child primary health care programmes. The study investigates the effectiveness of the strategy for controlling schistosomiasis in young children and mothers.

Specific objectives of freeBILy in Madagascar are as follows:
To assess the impact of TBST on child development by comparing schistosomiasis-associated growth and developmental disadvantages among young children in TBST sites (intervention) to those in non-TBST sites (control)To examine the impact of TBST on maternal health by comparing schistosomiasis-associated anaemia among young mothers in TBST sites to those in non-TBST sitesTo evaluate the sensitivity and specificity of the urine-based POC-CCA test for the detection of *S. mansoni* infections in routine maternal and child primary health care programmesTo conduct an economic evaluation of the TBST strategy in comparison with the status quo, including its impact on health-related quality of life and on the capacity to perform economic activities among pregnant and lactating women

### Trial design and location

freeBILy in Madagascar is a two-armed 40-cluster randomized phase III trial assessing the potential impact of TBST on child growth and maternal haemoglobin (Hb). The 40 study centres are located in areas of medium to high endemicity of *S. mansoni* in Madagascar with 20 sites in the Itasy and Bongolava regions west of Antananarivo and 20 sites in the Amoron’i Mania region north of Fianarantsoa. The coordination institutions for these centres are the universities of Antananarivo and of Fianarantsoa (Fig. 1).

**Fig. 1 Fig1:**
[figure not shown]
Distribution of the FreeBILy study sites across the regions of Bongolava, Itasy and Amoron’i Mania in Madagascar. In **A**, the geographic locations of these regions of Madagascar are depicted. In **B**, the full list of study sites and their distribution within the regions of Bongolava, Itasy and Amoron’i Mania are given

Figures 2 and 3 summarize the study design. According to the primary objectives, two different units of analysis exist: (i) children for whom the main outcome is the proportion showing stunted growth at 2 years of age and (ii) mothers for whom the main outcome is Hb level 2 years after delivery.

**Fig. 2 Fig2:**
[figure not shown]
Cluster randomized trial study design. The CSBs, randomly allocated between intervention and non-intervention, represent the randomization units. At the 5th or 6th month of pregnancy (T0), women will be enrolled in the study and consent for their children will be asked. At T0 and 9 (T3) and 24 (T4) months after birth, urine samples will be collected. At delivery (T2), children will formally become part of the study

**Fig. 3 Fig3:**
[figure not shown]
Design of the cross-sectional study. The two non-randomized CSBs Andina and Imerintsiatosika were selected as the intervention and non-intervention sites, respectively. At the 5th or 6th month of pregnancy (T0), women will be enrolled in the study and consent for their children will be asked. At T0, blood, urine and stool samples will be collected. At the end of the study, the sample will be analysed with the tests described in Table 3. At 8 months of pregnancy (T1) and 9 (T3) and 24 (T4) months after birth, urine samples will be collected. At delivery (T2), children will formally become part of the study

The units of randomization are the PHCC, called *Centres de Santé de Base* (CSB). There is a total of 23 CSBs in the Antananarivo and 49 CSBs in the Fianarantsoa study area. On the basis of the criteria listed in Table 1, 20 CSBs from the Antananarivo region (10 intervention and 10 control arms) and 20 CSBs from the Fianarantsoa region (10 intervention and 10 control arms) were selected. In addition to these 40 randomized CSBs, two non-randomized CSBs have been included in the trial: one is assigned to the intervention arm (Andina) and the other to the control arm (Imerintsiatosika). Objectives 1 and 2 are rolled out in the 40 randomized CSBs. Objectives 3 and 4 are rolled out in the two non-randomized CSB.

**Table 1 Tab1:**
[figure not shown]
Inclusion criteria for the selection of CSB (Centre de Santé de Base). For all the CSBs, the mentioned criteria were assessed and on the basis of the best scoring the final 42 centres were selected

### Study setting

freeBILy in Madagascar is being implemented into routine maternal and child primary health care programmes, which consist of ante- and post-natal care, child routine examination and vaccination. In Madagascar, these programmes are established at CSBs, which are at the lowest administrative level of the health care system providing high accessibility to the population.

### Intervention

In study centres of the intervention arm, the POC-CCA-TBST is being implemented among pregnant women between week 20 of pregnancy and delivery and at 9 months after delivery and among their babies at 9 months of age. The urine-based POC-CCA-test is done, and PZQ treatment is offered in case of a positive diagnosis. In the study centres of the control arm, no TBST is carried out, and in case of clinical suspicion of schistosome infection, the participants are referred to the local health system. At the 24 months’ time point, TBST is being applied in both arms.

### Randomization

Randomization was done at the CSB level. For randomization, a list with the codes of the 20 CSBs in the regions of Bongolava and Itasy (so-called Antananarivo sites) and 20 CSBs in the region of Amoron’i Mania (so-called Fianarantsoa sites) was provided to the Leiden University Medical Center (LUMC), which randomly allocated 10 of the sites to control and 10 to intervention arm stratified by regions. LUMC informed the University of Antananarivo, University of Fianarantsoa and BNITM about the randomization result.

While blinding at the CSB level is not possible, all procedures of the study and of TBST (including urine sampling) are implemented at both the intervention and control CSBs. Only the actual POC-CCA test and the treatment of positives are exclusively done in intervention sites. In the participant ID, an alphanumeric element will define the recruitment site of the women. In case women would change the study site during the course of the study, the study nurses would be able to identify the non-correspondence of the site from the participant ID. This ensures that the randomization scheme is kept.

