### Eligibility criteria

Eligibility criteria for the inclusion and/or exclusion of candidate participants are listed in Table 2. After information sessions at the research sites, eligibility criteria are preliminarily assessed for interested candidate participants. After the assessment, informed consent is requested to proceed with formal recruitment, which will start exclusively when informed consent is properly understood and signed by the participant. Informed consent will be obtained, from the participant or legal guardians of under 16 years old volunteers, by the study nurses who will enrol formally the participants just after signature.

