**Table 3 Tab3:**
[figure not shown]
Scheme of scheduled visits. T0 mothers enrolment at 5^th^ or 6^th^ month of pregnancy pregnancy; T1 pre-delivery follow up at the 8^th^ month of pregnancy; T2 delivery follow up at birth and inclusion of children; T3 follow up 9 month after delivery; and, T4 final follow up 24 months after delivery

T0: mother’s enrolment during the 5th or 6th month of pregnancy. Haemoglobin is measured on-site using the Hemocue® system, and a urine sample is being collected (≥ 25 ml). In the TBST intervention arm, the POC-CCA to test for schistosomiasis infection is done on-site. Women who test positive are offered (40 mg/kg) PZQ treatment. Additional samples (Table 4) are being collected at the non-randomized sites for the cross-sectional sub-study to assess the sensitivity and specificity of the POC-CCA test against a panel of reference tests described in Table 4.T1: 1st follow-up, 8th month of pregnancy. Haemoglobin is measured on-site by means of the Hemocue® system.T2: 2nd follow-up, delivery and child enrolment. The case report form (CRF) is completed. The newborns are included, unless the mother decides to withdraw her/him from the study. Weight and height of the newborns are measured.T3: 3rd follow-up, 9 months after delivery/birth. Haemoglobin is measured for all women using the Hemocue® system. Height and weight are measured for all children. A urine sample is being collected (≥ 25 ml) from all mothers and children. In the TBST intervention arm, the POC-CCA to test for schistosomiasis infection is being performed on-site for the mother and child. To test-positive mothers, a 40 mg/kg dose of PZQ treatment is offered. Test-positive children are treated with 300 mg.T4: 4th follow-up, 24 months after delivery/birth. Haemoglobin is measured for all mothers on-site using the Hemocue® system. Height and weight are measured for all children. A urine sample is being collected (≥ 25 ml) from all the women and children. In both arms, the POC-CCA test for schistosomiasis infection is being performed on-site for the mothers and children. All positive women and children are offered 40 mg/kg and 300 mg PZQ treatment, respectively.

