The recruitment of pregnant women ended on 4 February 2020. So far, pregnant women are predominantly showing interest in the study and in the possibility of receiving the treatment during pregnancy. Our findings will be discussed with the local authorities in order to promote the integration of such strategy in national guidelines if the results will prove a positive impact on the target populations. If results will prove the effectiveness of the interventions, they could be easily translated to other countries where the endemic context of schistsomiasis is comparable to the one of Madagascar. Overall, our findings will contribute to an improved evidence base for the elimination strategy of schistosomiasis.

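### Women enrol after open CSB allocation with a different offer by arm, so who enrols may depend on arm; the participant-ID check cannot detect this, and the stated primary tests do not adjust for it

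*Protocol article*

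**What the plan says.** **Allocation and openness.** The Fig. 2 caption states: "The CSBs, randomly allocated between intervention and non-intervention, represent the randomization units". Under Randomization, "LUMC informed the University of Antananarivo, University of Fianarantsoa and BNITM about the randomization result", and the same section opens its paragraph on blinding with "While blinding at the CSB level is not possible".

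**What differs by arm.** Visits and urine sampling are the same in both arms, but "Only the actual POC-CCA test and the treatment of positives are exclusively done in intervention sites". The T0 entry of the visit schedule (Data collection plan) adds: "In the TBST intervention arm, the POC-CCA to test for schistosomiasis infection is done on-site". Under Intervention, control participants with clinical suspicion of infection are referred to the local health system, and both arms receive test-based treatment at 24 months.

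**How women enter.** Under Eligibility criteria, after information sessions at the sites, "eligibility criteria are preliminarily assessed for interested candidate participants". Study nurses then take consent and enrol. The Discussion reports that "pregnant women are predominantly showing interest in the study and in the possibility of receiving the treatment during pregnancy".

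**The safeguard.** The participant ID carries a code for the recruiting site, so nurses can see a mismatch if a woman changes site during the study. The article concludes: "This ensures that the randomization scheme is kept". According to the Data collection plan, the ID is assigned at enrolment.

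**The analysis.** Analysis for the primary outcomes names chi-square tests and t-tests for stunting and t-tests for maternal Hb. Mixed-effects models are additional analyses, and their stated purpose is to handle between-cluster variation.

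**The concern.** Randomising CSBs makes the CSBs comparable in expectation. It does not make the enrolled women comparable if recruitment comes after allocation, the arm is visible, and the offer differs. A woman who suspects infection has a reason to enrol at an intervention CSB that she does not have at a control CSB. Conversely, women at control CSBs may decline more selectively.

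Choosing a CSB by arm is not far-fetched. Trial design and location gives 23 CSBs in the Antananarivo study area, of which 20 were randomised, 10 per arm. Distances cannot be judged, because Fig. 1 is not shown.

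Selection of this kind would affect both primary endpoints. A reader who takes the ID sentence at face value would believe that the matter is closed, and the stated primary tests compare the arms without any baseline adjustment.

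**Working it through.** **1. Was the arm known at recruitment?** The article gives no randomisation date. It does say that the on-site test and the treatment offer take place at the enrolment visit in intervention CSBs only. The arm was therefore known at the site when women were recruited.

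**2. What can the ID detect?**

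| Event | ID evidence |
|---|---|
| Woman enrols at one CSB and later attends another | Site code does not match: detectable |
| Woman chooses an intervention CSB before enrolment | Site code matches: not detectable |
| Woman declines at a control CSB | No ID exists: not detectable |

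**3. The plan's own figures.** Inputs are from Sample size and statistical analysis: 20% against 10% stunted, alpha 0.05 (two-sided assumed), design effect 1.9, inflation 1.3 × 4 = 5.2.
- Per arm: (1.960 + 0.842)² × (0.16 + 0.09) / 0.10² gives 197, so 394 in total at 80% power. With 1.282 in place of 0.842 it gives 263, so 526 at 90%. Both match the article.
- 394 × 1.9 = 748.6 (stated 749). 526 × 1.9 = 999.4 (stated 1000).
- 749 × 5.2 = 3895 and 1000 × 5.2 = 5200. The planned 4200 gives 4200 / 5.2 = 808 infected, or 808 / 1.9 = 425 effective, and about 82.5% power.

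The sample size reproduces and is not in dispute here.

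**4. Illustration if all children are analysed.** Prevalence of 25% is from the article. The 30% / 20% split is assumed. Take 10% stunting in the uninfected and 20% in the untreated infected.

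*Treatment removes the whole excess (treated infected = 10%):*
- Balanced: control 0.25 × 20 + 0.75 × 10 = 12.5; intervention 10; difference 2.5 points.
- 30% intervention, 20% control: control 0.20 × 20 + 0.80 × 10 = 12.0; intervention 10; difference 2.0 points. The shift is 0.5 / 2.5 = 20%.

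*Treatment has no effect:*
- Control 12.0; intervention 0.30 × 20 + 0.70 × 10 = 13.0. The arms differ by 1.0 point when the true difference is 0.

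*Other reading (20% in all untreated children, infected or not; 10% in treated infected):*
- Balanced: 20 − (0.25 × 10 + 0.75 × 20) = 20 − 17.5 = 2.5 points.
- 30% / 20%: 20 − (0.30 × 10 + 0.70 × 20) = 20 − 17 = 3.0 points. The same imbalance now inflates the effect.

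**5. Illustration if only the infected are analysed.** An imbalance in prevalence then drops out. Infected women who volunteer may still differ by arm. The table assumes that selection shifts baseline stunting risk, with about 213 effective per arm (425 / 2) and clustering already allowed for.

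| Shift (points) | Rejection rate, no true effect, two-sided 5% | Power at 20% v 10%, shift against intervention |
|---|---|---|
| 0 | 5.0% | 82.5% |
| 1 | 5.8% | 72.9% |
| 2 | 8.2% | 61.5% |
| 3 | 12.5% | 49.4% |
| 5 | 27.3% | 27.3% |

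The shifts are not from the documents. They show sensitivity, not an estimate.

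**The case against.** **The ID sentence is about site changes.** It follows directly on a sentence about women who move during the study. A reader might infer that the article claims the ID prevents selective volunteering; it does not say so. What remains is that the conclusion is worded for the randomisation scheme as a whole, so limiting the sentence is enough.

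**Several stronger readings go beyond the text.**
- That unblinded nurses judged eligibility: the article names nurses only for consent and enrolment and does not say who assesses eligibility.
- That treatment is what draws women in: the Discussion names interest in the study as well, with no breakdown by arm.
- That control women are never offered treatment: they receive test-based treatment at 24 months and are referred on clinical suspicion before that.
- That women crossed from control areas: the eligibility criteria (Table 2) are not shown, so a residence rule cannot be excluded.

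**Size and direction.** It is tempting to say that a 30% / 20% split moves the result by 1.0 point, or 40% of the 2.5-point effect, against the intervention. That figure ignores that the extra infected women in the intervention arm are treated. If treatment removes the excess, the shift is 0.5 point (20%), and under the other reading of the 20% figure the sign reverses.

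**Analysis population.** The sample size section says that analyses focus on infected women; the analysis section states no such limit. Under restriction, the prevalence mechanism and the value of adjusting for infection status both vanish. This objection stands, but differential volunteering among infected women is untouched.

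**Matters for a fuller document.** A baseline table and a catchment sensitivity analysis may sit in the full protocol or SAP, and their absence here is no fault. The primary tests are different: the article states them, and they are unadjusted.

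**Conclusion.** The point holds as a risk. Women are enrolled after open allocation, with testing and treatment before 24 months offered only at intervention CSBs. The one safeguard named acts only after enrolment, and the stated primary tests do not adjust for T0 differences.

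Nothing in the documents shows that selection occurred, and the direction is unknown. Identical visits and sampling reduce the difference between arms but do not remove it.

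For an assumed 10-point imbalance in T0 infection with all children analysed, the distortion is 0.5 point on a 2.5-point effect if treatment removes a 10-point excess, and 1.0 point if treatment does nothing. With an infected-only analysis that mechanism disappears, and the size depends on how far infected volunteers differ by arm, for which the documents give no figure. The change is worth making but does not call the design as a whole into question.

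**What to change.** 1. **Randomization section.** Limit the closing sentence to what the ID does: it lets staff detect a participant who attends a different CSB after enrolment.

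2. **Analysis for the primary outcomes.** Replace the unadjusted chi-square and t-tests as the primary analysis of both endpoints with a cluster-aware comparison. This can be the mixed model now listed as additional, or a cluster-level equivalent. Prespecify these covariates:
   - T0 laboratory POC-CCA/CAA infection status, if all women are analysed. The Table 5 caption plans these assays on T0 samples from all women at all sites, so the covariate is measured alike in both arms.
   - T0 Hb for the maternal Hb endpoint, in either population. The T0 visit already includes it.

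**Cost.** Revised wording and a change of primary model, using data already planned. Missing T0 laboratory results need a stated rule, such as a missing category. Recruitment closed on 4 February 2020, so the recruitment process cannot be altered. Adjustment deals only with what was measured at T0, and some selection may remain.
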